### Data collection

Data will be collected at RACF, resident and pharmacist levels throughout the 12-month trial period. RACFs’ characteristics (number of beds, number of permanent residents, resident profile and number of staff) will be collected through surveys with RACF managers. De-identified residents’ data for outcome measures will be collected by the research team visiting the facilities at baseline, each month and at 12 months. Randomly selected medication rounds will be observed to determine the time spent on medication rounds and assess the appropriateness of dose form modifications using the method described earlier [47]. In case of potential logistical limitations in light of COVID-19 and any future restriction of access to RACFs, RACF staff will collect the required data. On-site pharmacists in the intervention group will self-report their daily activities through an online diary using QUALTRICS. Details of data collection items and timing are listed in Table 2.

**Table 2 Tab2:** Data collection details

Data	Data collection

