#### Pharmacists

Qualified pharmacists will be recruited through open expressions of interest sent to pharmacy professional groups and associations. The selection criteria for pharmacists include having registration with the Australian Health Practitioner Regulation Agency, accreditation to conduct medication reviews by the Australian Association of Consultant Pharmacy or equivalent hospital or geriatric clinical pharmacy experience, and accreditation to conduct vaccination. A list of eligible pharmacists will be provided to the intervention RACFs, who will employ pharmacists as per their organisational policy. Salaries for pharmacists will be funded by the research grant; however, they will be directly employed by RACFs as RACF staff members.

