### Randomisation and blinding

Randomisation will be at the facility level. RACFs will be randomised into either intervention or control group through computer-generated allocation by an independent researcher external to the research team. Randomisation will be stratified by size of facility. Due to the nature of the intervention, the trial participants will not be blinded.

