#### Secondary outcomes

Rate of unplanned ED presentations and hospital admissions per resident collected from RACF records over 12 monthsPolypharmacy—number of regular medicationsChange in proportion of residents who are prescribed at least one psychotropic medicine (defined as antipsychotics and benzodiazepines), excluding those residents with major psychiatric diseases or epilepsy (from baseline to 12 months)Change in dose of psychotropic medicines (measured as chlorpromazine or diazepam equivalent daily dose [55] (from baseline to 12 months)Change in residents’ Anticholinergic Cognitive Burden Score (ACB) [56] (from baseline to 12 months)Rate of staff influenza vaccination measured at the end of influenza season, from RACF recordsFall rate per resident, as documented from RACF fall records over 12 monthsChange in time spent on medication administration rounds per RACF, through observing randomly selected medication rounds [47] (from baseline to 12 months)Change in appropriateness of medicine dose form modification per RACF, through observing randomly selected medication rounds [47] (from baseline to 12 months)Change in proportion of residents who have drug allergies or adverse drug reactions documented in their RACF records (from baseline to 12 months)Number of medication-related incidents over 12 monthsCost-consequence and cost-effectiveness of the intervention over 12 months

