**Resident level data**	
Age and gender	Baseline
Date of admission and discharge and reason for discharge from the facility	Baseline and monthly
Diagnosis	Baseline and at 12 months
Number and list of regular and PRN medications including dosages	Baseline and at 12 months
Emergency Department visit/transfer*	Baseline and monthly
Hospital admissions* and length of hospital stay as determined by RACF residents’ records	Baseline and monthly
Reason for Emergency Department visit/admission to hospital - as determined by RACF residents’ records	Baseline and monthly

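### The fallback rule lets intervention pharmacists collect outcome data in one arm only, and the psychotropic exclusion is not tied to the baseline diagnosis

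*Protocol article*

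**What the plan says.** **Who collects.** The Data collection section makes the research team the normal collector: "De-identified residents’ data for outcome measures will be collected by the research team visiting the facilities at baseline, each month and at 12 months". It then provides for COVID-19 and later limits on access, in which case "RACF staff will collect the required data". No group of staff is excepted. The Pharmacists section says of the intervention pharmacists that "they will be directly employed by RACFs as RACF staff members". Control facilities continue usual care with visiting pharmacists (Study design; Table 1) and have no such employee.

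**Masking.** Randomisation and blinding contains one statement: "Due to the nature of the intervention, the trial participants will not be blinded". It does not mention collectors or coders in either direction.

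**The psychotropic denominator.** The secondary outcome is the change in the proportion of residents on an antipsychotic or benzodiazepine, "excluding those residents with major psychiatric diseases or epilepsy". Table 2 lists diagnosis as collected at baseline and again at 12 months. The outcome definition does not say which of the two decides the exclusion. The list of pharmacist activities under Intervention and model of care includes updating and improving residents' clinical and care records.

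**The concern.** There are two separate weaknesses.

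First, the contingency names its collector too loosely. Read literally, it admits the on-site pharmacist, who has an interest in the result. That pharmacist is also given the Beers Criteria as a training resource (Pharmacist training and support), and the Beers Criteria are the instrument for the primary outcome. Because the role exists only in intervention facilities, the collection process could differ by arm. The contingency is not remote: the Discussion expects that visiting restrictions may affect data collection.

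Second, if a diagnosis recorded after randomisation can decide who is counted, then the denominator can respond to the intervention. This needs neither a pandemic nor any impropriety. Careful record-keeping by the pharmacist would be enough, and research staff copying the record faithfully would carry the change into the data. At stake is whether a between-arm difference in psychotropic prevalence reflects prescribing or recording.

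**Working it through.** The protocol gives no figure on this point, so there is none to reproduce.

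**Collector: the passages side by side**

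- The fallback collector is any facility staff member (Data collection).
- The intervention pharmacist is a facility staff member (Pharmacists).
- The control arm has no on-site pharmacist (Study design).
- The fallback therefore admits the deliverer of the intervention as collector in one arm and cannot do so in the other. No sentence in the article closes this off.

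**Denominator: the arithmetic**

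Let *p* be psychotropic prevalence among eligible residents at 12 months. Let *u* and *v* be the shares of users and of non-users who acquire an excluding diagnosis in the record during the trial. With no drug stopped or started, the recorded prevalence becomes

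p′ = p(1 − u) / [p(1 − u) + (1 − p)(1 − v)].

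Assumed inputs: 600 eligible residents in the arm (a round figure near the planned 594 per arm) and 200 users, so p = 33.3%. The documents give no value for *u* or *v*.

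| Reclassified | Calculation | Recorded prevalence |
|---|---|---|
| None | 200/600 | 33.3% |
| 5% of users | 190/590 | 32.2% |
| 10% of users | 180/580 | 31.0% |
| 20% of users | 160/560 | 28.6% |
| 10% of users and 10% of non-users | 180/540 | 33.3% |
| 10% of non-users only | 200/560 | 35.7% |

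The shift depends on *u* differing from *v*. When they are equal the ratio is unchanged; when *v* exceeds *u* the recorded prevalence rises.

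**Sensitivity to the starting prevalence**

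Let *r* be the share of all eligible residents who are users and are newly excluded, with no non-users excluded. Then p′ = (p − r)/(1 − r).

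| p | r = 2% | r = 5% | r = 10% |
|---|---|---|---|
| 20% | 18.4% | 15.8% | 11.1% |
| 40% | 38.8% | 36.8% | 33.3% |
| 61% | 60.2% | 58.9% | 56.7% |

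The 61% is the prevalence of psychotropic use in the large Australian cohort cited in the Background. It may cover more drug classes than the trial's definition. The other values of *p*, and every *r*, are assumptions.

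**From the 12-month proportion to the change score.** If each time point uses its own diagnoses, the whole shift enters the change from baseline. If 12-month diagnoses are applied to both time points, residents who were users at both are removed from both and much of the shift cancels, although selection then still rests on a post-randomisation variable. If baseline diagnoses are used, the mechanism disappears.

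**The case against.** The article condenses a fuller protocol (Trial status cites version 3) that is not shown, and assessor masking and coding rules are commonly left to such a document. That stands: the article's silence on assessor masking is not a finding. A reader might infer that outcomes are collected unmasked, but the blinding statement concerns participants only.

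Research staff are the default collectors, and nothing assigns outcome collection to pharmacists. Data collection gives them an activity diary instead, Data management has facility staff only helping research staff, and Fidelity assessment lists staff and pharmacists separately. This makes it less likely that the literal reading was intended. It does not remove that reading, because the Pharmacists section expressly makes them staff members.

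A reader might also infer a bias in the primary outcome. The documents do not support a figure for it. Table 2 collects medication lists with doses, not a judgement of inappropriateness, and the Discussion describes the Beers Criteria as explicit, reliable and reproducible. Any assumed misclassification rate would be conjecture.

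On the denominator, a baseline definition fits the text as well as a 12-month one. New diagnoses may also be recorded in control facilities, and the activity list does not mention psychiatric or epilepsy diagnoses. All of this is fair, and it is why the effect is conditional. The ambiguity remains, and one reading lets the intervention influence who is counted.

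**Conclusion.** The point holds in a limited form. As written, the contingency permits the deliverer of the intervention to collect its outcome data in one arm only. The psychotropic exclusion does not fix a diagnosis time point, although diagnoses are collected twice and record updating is part of the intervention.

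The size of the second effect rests wholly on assumptions. With 200 users among 600 residents and 5% to 20% of users reclassified, recorded prevalence falls by 1.1 to 4.7 percentage points (33.3% to 32.2% and 28.6%) with no prescribing change. This requires 12-month diagnoses to be used and new diagnoses to fall mainly among users at intervention sites. If users and non-users are reclassified equally, the effect is zero.

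A reader might conclude that the trial's comparisons are biased toward the intervention in general. That is not shown. Fuller recording of falls, incidents or emergency transfers at intervention sites would count against the intervention, and the Discussion already concedes that facility records may under-report. What is supported is a gap in protection for data collected under the contingency and for one secondary outcome.

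**What to change.** 1. State in Data collection that on-site pharmacists take no part in collecting or coding trial outcomes. Under the contingency, another staff member supplies the medication charts as they stand.
2. Define the psychiatric and epilepsy exclusion, in both arms, by the diagnosis recorded at baseline. Use the diagnosis recorded at admission for residents who enter later, since Statistical analysis includes them. Table 2 has no admission time point for diagnosis, so this would have to be read from the admission record.
3. Where feasible, have the research team code potentially inappropriate medicines from medication lists with facility and arm removed. The data are already de-identified at resident level, so the extra step is to remove the facility and arm labels.

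Masking of dose-form appropriateness is not asked for: it is judged by observing medication rounds on site, and nothing in the article shows that masking would be workable.

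The first two changes take about a sentence each. The third costs a small amount of data-handling time. None alters the intervention, the sample size or the outcome set.

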**Facility level data**	
Number of permanent residents, proportion of residents with dementia, and proportion receiving the highest level of government funding	Baseline and at 12 months
Number of RACF registered nurses rostered during day/night/weekend	Baseline and at 12 months
Care staff turn-over reported by RACFs	Baseline
Total number of beds and bed occupancy rate	Baseline
Resident turn over	Monthly
Number of medication-related incidents	Monthly
Number of resident falls	Monthly
Time taken to conduct medication rounds	Baseline and at 12 months
% of staff/residents received influenza vaccination	At one time point
% of residents that have drug allergy and adverse drug reactions documented	Baseline and at 12 months
Number of GPs visiting residents in facility	Baseline
RACF managers perceived top 5 reasons for unplanned hospitalisations of residents in previous 12 months, and possible solutions for reducing these	Baseline

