### Sample size

It was estimated that a conventional RCT with randomisation of individuals would be able to detect a reduction from 60 to 40% of residents having at least one PIM [14], with a minimum of 106 residents in each arm (total of 212 residents in both arms) with a significance level of 5%, a power of 80% on equal allocation and a response rate of 85%. By adjusting for the loss of power due to clustering, with an intra-cluster correlation coefficient of 0.05 and a cluster size of 93 residents per RACF, the estimated sample size is (1 + [(93–1) x 0.05] =5.6 x 106) or 594 residents in each arm (1188 in both arms), equating to a minimum of 13 sites. The sample size was calculated using G*Power 3.1.9.4 [57].

The estimated prevalence of PIM in RACFs at baseline (60%) was based on previous studies in which the prevalence of PIM in Australian RACF residents were reported as 73% in 2018 [16], 49% in 2014 [14] and 56% in 2012 [58].

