### Statistical analysis

Descriptive statistics will be used to summarise and compare the data at the RACF level in each group at baseline and at the end of the trial, including primary and secondary outcomes as well as additional potential confounder variables (such as demographic profile, duration of residency, presence of dementia, Charlson comorbidity index [59] and number of medical conditions).

Bivariate analyses for group comparisons will use either t tests or ANOVA for data that are normally distributed, Mann-Whitney U and Kruskall-Wallis tests for data that are not normally distributed, or chi-square-based analysis for categorical outcome data. For within group comparisons, paired t tests and repeated measures ANOVAs will be used; if variables are not normally distributed, the Wilcoxon signed-ranks and Freedman tests will be used, while the McNemar test will be used for changes in proportions.

To determine the effect of the intervention on the outcome measures and the changes over time (between-within group effects), multilevel modelling methods, which take into consideration the hierarchical structure of the data (including clustering within RACF and repeated measurement occasions) will be applied. These modelling methods will include mixed-effects generalised linear models (Logistic and Poisson regression models) for binary and count outcomes as well as mixed-effects linear models for continuous outcomes assumed to have a normal distribution, or otherwise transformed to meet the assumption.

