Analysis will be weighted by cluster size as required. Interactions and adjusting for demographic characteristics and other potential covariates will be included when deemed necessary. Residents who enter, die or move from RACFs after baseline data collection will have only one data point and will be included in the analysis. When data are missing at random, patterns of missing data will be evaluated, and potential predictors of missing responses will be investigated. Methodological attempts to fill in missing data will be extensively explored and applied as appropriate. These include single imputation approaches (such as regression imputation and nearest neighbours or hot-deck imputation) and multiple imputation approaches. Analysis will be conducted using either SPSS version 26 or STATA version 16. Significance level will be set at the usual 5% alpha-level (two-tailed where applicable). All estimated effects will be reported along with their 95% confidence intervals.

Since the sample size and power calculation have been devised based on the primary outcome and hypothesis, the level of adjustment and number of potential covariates to adjust for may be limited by the sample size and the response rate. Posterior power calculations will be performed based on available sample size and the secondary outcomes.

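### Table 2 collects no pre-intervention value for falls, medication incidents or staff influenza vaccination, so precision is lost and the baseline comparison promised for secondary outcomes cannot be made for these three

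*Protocol article*

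**What the plan says.** The Secondary outcomes list defines falls as a rate per resident over 12 months, medication-related incidents as a number over 12 months, and staff influenza vaccination as a rate at the end of the influenza season. None of the three is worded as a change from baseline, whereas most of the other outcomes are.

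Table 2 matches those definitions. Under facility level data, "Number of resident falls" and medication-related incidents are marked *Monthly*, and influenza vaccination has one time point. Emergency department visits and hospital admissions, by contrast, are marked *Baseline and monthly*. Medications, medication-round time and allergy documentation are collected at baseline and at 12 months.

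The Statistical analysis section says that descriptive statistics will compare facility-level data "in each group at baseline and at the end of the trial, including primary and secondary outcomes". It then plans multilevel models that allow for clustering within facility and for repeated measurement.

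On design, "Randomisation will be at the facility level" and "Randomisation will be stratified by size of facility". The Sample size section arrives at 1188 residents, "equating to a minimum of 13 sites".

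**The concern.** The analysis text presupposes a baseline value for every secondary outcome, and the data schedule does not supply one for three of them. This gap lies in data collection. A later analysis plan can choose a model, but it cannot adjust for a prior rate that nobody recorded.

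It matters because few facilities are randomised and size is the only stratification factor. Fall rates, incident counts and vaccination uptake can be expected to differ between facilities through case mix, local practice and recording habits. The Discussion itself concedes that facility records may under-report. A facility's own earlier rate is usually the best single predictor of its later rate. Without it, the confidence interval is wider than it need be, and a reader of the results cannot tell whether the arms started level.

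The three outcomes are not peripheral. Higher staff vaccination was a reported pilot finding, improving vaccination is a listed pharmacist activity, pharmacists sit on the falls and medication-incident review committees, and the secondary outcomes feed the cost-consequence analysis.

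**Working it through.** **1. The plan's own figure.** The design effect is 1 + (93 - 1) × 0.05 = 5.6. Then 106 × 5.6 = 593.6, rounded up to 594 per arm and 1188 in total; 1188 / 93 = 12.8, so 13 facilities. This reproduces the stated minimum. The calculation assumes equal allocation ("with a significance level of 5%, a power of 80% on equal allocation and a response rate of 85"), which gives 6 v 7 facilities.

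**2. Inputs not in the documents.** These are assumptions: between-facility coefficient of variation (CV) of the rate, 0.3 to 0.5 (0.2 also tried); correlation *r* between a facility's prior and follow-up rates, 0.5 to 0.8, with 0.7 as the working value; 2 falls per resident-year; between-facility standard deviation (SD) of staff vaccination, 10 to 20 percentage points.

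**3. Chance spread of the rate ratio when there is no effect, from facility differences alone.** SE(log RR) = CV × √(1/6 + 1/7) = CV × 0.556. A prior-rate covariate multiplies the SE by √(1 - r²). At r = 0.7 this is √0.51 = 0.714, so 49% of the variance is removed. The 95% range is exp(±1.96 × SE).

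| CV | SE, no prior rate | 95% range | SE, r = 0.7 | 95% range |
|---|---|---|---|---|
| 0.3 | 0.167 | 0.72-1.39 | 0.119 | 0.79-1.26 |
| 0.4 | 0.223 | 0.65-1.55 | 0.159 | 0.73-1.37 |
| 0.5 | 0.278 | 0.58-1.72 | 0.199 | 0.68-1.48 |

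At r = 0.5 the remaining variance is 75%, and at r = 0.8 it is 36%.

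**4. More facilities than the minimum.** The 1978 beds in the region allow at most about 1978 / 93 = 21 facilities, or 10 v 11. Then √(1/10 + 1/11) = 0.437. The range is 0.77-1.29 at CV 0.3 (0.83-1.20 with the covariate) and 0.65-1.53 at CV 0.5 (0.74-1.36). The proportional gain is the same.

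**5. Power for a 30% reduction in falls, 6 v 7 facilities.** SE = √[(ln(1 + CV²) + 1/(2 × 93)) × (1/6 + 1/7)], with *t* on 11 df, or on 10 df once the covariate is added. The test is two-sided at 5%, in line with "Significance level will be set at the usual 5% alpha-level (two-tailed where applicable".

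| CV | No prior rate | With prior rate, r = 0.7 |
|---|---|---|
| 0.2 | 79% | 97% |
| 0.3 | 49% | 76% |
| 0.4 | 32% | 54% |
| 0.5 | 23% | 40% |

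**6. Staff vaccination.** The 95% confidence half-width is t × SD × 0.556, with t = 2.20 (11 df); with the covariate, t = 2.23 (10 df) and the SE is multiplied by 0.714. At SD 10, 15 and 20 points it falls from 12.2 to 8.9, from 18.4 to 13.3 and from 24.5 to 17.7 points.

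**7. Type I error.** In 20,000 simulated trials of 6 v 7 facilities with no effect, at each CV from 0.2 to 0.5, a facility-level *t* test rejected in 4.7% to 5.1%. A Poisson comparison that ignored facility rejected in 50% to 78%.

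**The case against.** The strongest reply is that nothing here is biased. Allocation is by facility, the effect analysis is multilevel, and chance differences between facilities are therefore carried into the confidence interval. This stands. A reader might infer from the wide ranges in the working that ordinary facility differences will be mistaken for an intervention effect. The documents do not support that: with facility accounted for, false positives stay near 5%, and the 50% to 78% figures arise only if facility is ignored, which the planned effect models do not do.

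A reader might also infer that the planned models cannot be fitted to these outcomes. That is too strong as well. Monthly counts give repeated occasions for falls and incidents, and a time trend within follow-up can be estimated. Only vaccination has a single value. What is missing is the pre-intervention level.

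The post-only outcome definitions agree with Table 2 and look deliberate, and the conflicting sentence is a general one about descriptive statistics. That narrows the contradiction without removing it, since the sentence names secondary outcomes without exception. Nor does reading a baseline into *Monthly* work well, because the same table writes *Baseline and monthly* where that is meant. The Data collection text does mention baseline collection of residents' outcome data, but Table 2 lists these three items as facility level data.

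Imbalance is not wholly invisible either. Size is stratified; dementia proportion, funding level, nurse rostering, staff turnover, age, gender and diagnosis are collected at baseline, and covariate adjustment is allowed. Part of the case mix can therefore be handled. The facility's own prior rate cannot.

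Finally, the magnitudes rest on assumed values, and 13 is a minimum. Both points stand.

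**Conclusion.** The point holds as a loss of precision and a mismatch between two sections. For falls, medication incidents and staff vaccination, the baseline comparison promised in the Statistical analysis section cannot be produced from the Table 2 schedule, and no prior rate will be available for adjustment. The randomised comparison remains valid.

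Under the assumed CVs of 0.3 to 0.5 and correlation of 0.7, the avoidable part is about half of the between-facility variance. A weaker correlation shrinks the gain (a quarter of the variance at 0.5) and a stronger one enlarges it (64% at 0.8). None of these values comes from the documents.

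Three of the twelve listed secondary outcomes are affected. The primary outcome has a baseline and is untouched. This is a worthwhile, inexpensive improvement and not a flaw that threatens the trial's main conclusion.

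**What to change.** Amend Table 2 in three rows:

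- **Falls and medication incidents:** add a retrospective prior-period count from facility records (for example the previous 12 months), with resident-days or occupied beds for the same period, and keep the monthly collection.
- **Staff influenza vaccination:** add the previous season's staff percentage from facility records.

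Fix the reference period in advance, end it before the intervention starts, and extract it in the same way in both arms. Keep the outcome definitions as they are. In the multilevel models, enter each prior value as a facility-level covariate for its own outcome, and use the baseline emergency department and admission data already in Table 2 in the same way, which needs no new data. Table 2 and the Statistical analysis section then agree.

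The cost is a few figures per facility from records the team already visits, plus one degree of freedom per model (10 instead of 11 at 13 facilities). Being retrospective, it can be added although recruitment has begun. Some prior records may be incomplete, and the reference period may differ from the COVID-19 period in both arms. Either would reduce the gain without biasing the comparison.
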